#### School climate

Perception of school climate will be assessed via a questionnaire [101] completed by 30 school staff per school (equal proportion of teachers, support staff and administrators) chosen at random in year one. The same school staff in each school will subsequently complete the survey at the end of each project year. The questionnaire has four factors: Skill Instruction; Support for Staff; Staff Respect for Students; and Safety. We will use all four factors in the analyses.

#### Mental health disparities

We will measure changes in mental health disparities as a result of Tier 1 interventions by comparing scores on school climate and school suspension rates between year one (baseline) and each subsequent year across all schools. Changes in mental health services disparities as a result of Tier 2 interventions will be assessed via a semi-structured service utilization interview [102,103] administered to the parents of children in Tier 2 across all schools between the baseline and intervention phases.

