## Background

### Services disparities

Several epidemiologic studies have shown that only one in five children with emotional and behavioral disorders receive mental health services [1-3]. Low-income and ethnically diverse children lag well behind their middle class, Caucasian counterparts in rate of service utilization [3,4]. Access barriers, such as lack of specialized services in low-income communities, high cost,and poor service quality, and stigma have been found to affect service utilization by ethnically diverse children [5-9]. Service delivery strategies that address access barriers and minimize the effects of stigma are likely to reduce service disparities [10].

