### Study aims

The specific aims of the study are:

1. To determine whether program content and process fidelity for Tier 1 (for all students) and Tier 2 (for at risk and high risk students) differ between schools receiving a higher level of support (Consultation plus Coaching, C + C) and schools receiving a lower level of support (Consultation, C) for program implementers.

2. To determine whether school climate, office discipline referrals, and participants’ diagnostic status, symptom and impairment severity, coping skills, and academic productivity differ between schools receiving different levels of support (C or C + C).

3. To assess changes in mental health disparities brought about by Tier 1 (perception of school climate, student suspension rates) and Tier 2 (proportion of students with unmet need), respectively.

4. To determine the incremental cost-effectiveness of SWPBIS C versus SWPBIS C + C.

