## Methods/Design

Six K–8 schools in the School District of Philadelphia were randomly assigned to either Consultation or Consultation plus Coaching (See Figure 2). A stratified random assignment list of schools to condition was generated using a computerized random assignment program [77]. Schools were stratified to group one if their baseline School Climate (CREST) scores were below the median CREST scores or to group two if the CREST scores ≥ the median value. The units of analyses for Tier 1 are all of the students in those K-8 schools (650 per school), leadership team members (eight per school) and other school staff (30 per school). The units of analyses for Tier 2 are the children meeting criteria for inclusion in one of the GCBT groups (enroll a total of 367 students assuming a 17% dropout; approximately 51 eligible students per school), the school counselors (two per school) conducting the GCBT groups, and the groups themselves (14 per school; see Table 1).

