### Inclusion criteria

All children will participate in Tier 1. Children in grades 4–8, who meet screening and diagnostic criteria will be included in Tier 2. The screening criterion is a score ≥1 SD on the Conduct Problems or Emotional Symptoms scales of the Strengths and Difficulties Questionnaire (SDQ), a widely-used screening instrument [78], filled out by a teacher. Children meeting screening criterion will undergo a diagnostic evaluation. Children meeting primary diagnosis of ODD, CD, GAD, SAD, or SP (based on a parent structured interview [79] and a symptom severity scale [80] filled out by an independent rater) at Intermediate or Positive level will be eligible for participation. Children with comorbid (secondary) conditions will be included.

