### Setting

The SWPBIS project will be implemented in six K–8 public schools in North Philadelphia, PA, a low-income area that has the second highest level of food insecurity in the country [83]. The ethnic makeup of students is approximately 60% Latino, 30% African American, 10% other minority.

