### School recruitment

Upon receiving funding, a presentation of the project was conducted with a preselected group of school administrators from schools in the regional area of interest. Presentations were conducted in person and via GoToMeeting. Those who expressed interest in taking part in the project were asked to respond to a brief request for proposals (RFP). The six schools that applied met the minimal inclusion criteria, so the search was discontinued at this stage. The inclusion criteria included: grade level (any elementary or middle school combination); students’ socio-economic status (percentage of students eligible for free/subsided lunch set at ≥ 90%); racial/ethnic diversity (majority of students are of minority status); and school-wide initiatives (absence of current mental health prevention initiatives). A more in-depth description of the project was provided during staff meetings and a vote was taken. At least 80% of school staff in attendance was required to vote affirmatively in order for the school to join the project. This is a standard cut-off in SWPBIS [88]. Subsequently, the investigators trained members of the leadership teams. As of this writing, the leadership teams are developing interventions for Tier 1 while receiving C or C + C.

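### Aim three claims program-caused change in disparities, but its pooled before-after comparisons can only show change over time in six under-served schools that all receive the program

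*Protocol article*

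**What the plan says.** The third aim, under Study aims in the protocol article, is "To assess changes in mental health disparities brought about by Tier 1 (perception of school climate, student suspension rates) and Tier 2" (the Tier 2 indicator being the proportion of students with unmet need). The Mental health disparities section repeats the causal sense: "We will measure changes in mental health disparities as a result of Tier 1 interventions by comparing scores on school climate", together with suspension rates, between year one and each later year across all schools. It uses the same causal phrase for Tier 2.

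The Data analytic plan names the tests:
- climate scores against baseline by a two independent sample t-test;
- suspensions against baseline by a Chi-squared test;
- unmet need at baseline against later cohorts by a Chi-squared test.

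The design is given under Methods/Design, "Six K–8 schools in the School District of Philadelphia were randomly assigned to either Consultation or Consultation plus Coaching", and under Inclusion criteria, "All children will participate in Tier 1". The two arms differ in the external support given to school personnel; both deliver SWPBIS.

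The article's own idea of a disparity is in the Background: "Low-income and ethnically diverse children lag well behind their middle class, Caucasian counterparts in rate of service utilization". The Abstract opens with a similar contrast, urban against non-urban schools. On the study population, Setting says "The ethnic makeup of students is approximately 60% Latino, 30% African American, 10% other minority", and School recruitment lists the criterion "percentage of students eligible for free/subsided lunch set at ≥ 90" per cent.

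**The concern.** The stated aim and the planned contrast do not match, in two respects.

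First, as the article uses the word, a disparity is a difference between two populations. The planned analyses follow one population. A fall in suspensions in the study schools could accompany an equal or larger fall elsewhere, and the plan would still describe it as a change in disparities.

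Second, the wording is causal, but every school is treated and the arms are pooled, so the comparison does not use the randomization. Any change in district policy, leadership, discipline reporting or service supply over the project years would be counted as an effect of the tiers. Challenges and limitations reports repeated district leadership changes and staff turnover during the pilot. The limitations stated there concern generalizability and clustering, not this.

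At stake is the interpretation of the aim that carries the study's disparities rationale. The randomized comparison of the two support levels is not affected.

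**Working it through.** The article gives no sample size, power or effect size for aim three, so there is no figure to reproduce. The check sets the planned contrast beside the claimed quantity, then adds two illustrations on assumed inputs.

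**1. Claimed quantity against planned contrast.** Let S be an outcome level in the study schools and R the level in a reference population, at baseline (0) and year t.
- Change in disparity = (S_t − R_t) − (S_0 − R_0) = (S_t − S_0) − (R_t − R_0).
- Planned contrast = S_t − S_0.

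The two agree only if R_t − R_0 = 0. No R is collected for any of the three indicators.

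**2. Could the sample supply R?** By ethnicity, 60 + 30 + 10 = 100% minority (stated as approximate), so there is no majority group. By income, the lunch criterion leaves at most about 10% of students per school not eligible, that is 0.10 × 650 = 65 of about 650. No contrast by income or ethnic group is planned. School climate is rated by staff, 30 per school, and so does not divide into student groups.

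**3. Attribution.** Untreated schools: 0 of 6. The observed change S_t − S_0 is program effect plus background change: one observed difference, two unknowns.

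**4. Illustration: how readily would background change alone be significant?** Assumptions, none from the article: zero program effect, independent observations, two-sided alpha 0.05, suspension treated as a yes/no proportion, and the base rates and drifts shown. With mean proportion p̄ and n per year,

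power = Φ{ [d − 1.96·√(2p̄(1−p̄)/n)] / √[(p₁(1−p₁)+p₂(1−p₂))/n] }.

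For n = 3,900 (Table 1), p₁ = 0.10 and p₂ = 0.08: [0.02 − 1.96 × 0.00648] / 0.00648 = 1.13, and Φ(1.13) = 0.87.

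| Outcome (n per time point) | Assumed base | Assumed drift | Probability of p < 0.05 |
|---|---|---|---|
| Suspension (3,900) | 10% / 20% / 30% | 2 points | 0.87 / 0.62 / 0.50 |
| Suspension (3,900) | 10% / 20% / 30% | 3 points | 0.997 / 0.93 / 0.84 |
| Climate (180 staff) | – | 0.3 SD | 0.81 |
| Unmet need (102, assuming 306/3 per cohort) | 80% | 10 points | 0.38 |
| Unmet need (102) | 80% | 20 points | 0.88 |

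**5. Illustration: what a concurrent series would add.** Assume suspensions per 100 fall from 20 to 15 in study schools and from 12 to 7 elsewhere in the district.
- The plan reports 15 − 20 = −5.
- The difference in change is (15 − 20) − (7 − 12) = 0.
- The absolute difference stays at 8 (20 − 12 and 15 − 7), while the ratio rises from 20/12 = 1.67 to 15/7 = 2.14.

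These rates were chosen to show the mechanism and say nothing about what will happen.

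**The case against.** The strongest reply is that this is partly terminology. The aim lists its indicators, the analysis section says what is compared with what, and a careful reader can see that the result is change over time in under-served schools. Raising outcomes in such schools is legitimate disparities work. For Tier 2, unmet need (disorder present, no services received) is an absolute access deficit that can be interpreted without a second population. All of this stands, and it supports restating the aim rather than dropping it. It does not rescue the causal phrases, for unmet need or for the other two indicators.

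A second reply is that having no untreated arm follows from a comparative-effectiveness design, and that the Data analytic plan has a randomized support-by-time contrast for climate and discipline referrals. That is true, but the contrast isolates the level of support, not the tiers, and aim three does not use it.

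Three stronger readings are not supported:
- A reader might infer that every student is minority and low-income, so that no internal reference could exist. The lunch criterion is a school-level threshold of at least 90%, and the ethnic figures are approximate. The accurate statement is that no such contrast is planned.
- A reader might infer that secular change is known to have moved these outcomes. The leadership changes were in the pilot, and the article does not link them to suspensions, climate or service use.
- A reader might infer that other district schools would supply the missing disparity reference. The article does not describe those schools, and they are neither the non-urban schools of the Abstract nor the middle-class Caucasian children of the Background. They can serve only as a control for trend.

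**Conclusion.** The point holds as a mismatch between claim and analysis. The words "To assess changes in mental health disparities brought about by Tier 1" promise a causal change in a between-group gap. The fixed analyses deliver pooled before-after change in six treated schools. They can show whether climate, suspensions and unmet need changed there. They cannot show that a disparity changed, or that the program rather than background change was responsible.

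The size of the error is not estimable, because the document has no reference-group data. The probabilities and suspension rates in the working are illustrations on assumed inputs; they show only that a modest background change could often reach significance. The conclusion rests on the stated design, composition and tests, not on those figures. A change should be made before results are reported. Sample size and the primary outcome, diagnostic status under aim two, are untouched.

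**What to change.** 1. Restate aim three as change over time in school climate, suspensions and unmet need in under-served schools. In Study aims and in Mental health disparities, replace *brought about by* and *as a result of* with *after*.

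2. For suspensions, if the district can supply annual school-level rates (an assumption), add the same-year rates of its non-participating K–8 schools. Report, for each year, the study schools' change from baseline minus the comparison schools' change from baseline. Call this a control for secular trend, not the disparity gap of the Abstract or Background. The six schools applied to join and voted to do so, so the comparison is not randomized and supports attribution only in part.

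3. For climate and unmet need, where no concurrent series is collected, the rewording is the whole change.

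The cost is a more modest claim, some redrafting and one aggregate data request to the district. No new participants, visits or instruments are needed. If the data cannot be obtained, step 1 stands alone.

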### Child outcome measures for at risk/high risk children

Children’s diagnostic status, mental health symptoms, coping skills and functional impairment will be assessed at pre- and post-participation in CPP and FRIENDS. All of the parent measures are available in Spanish. Diagnostic status will be assessed via a computerized parent-structured interview [79,104]. This instrument reports three levels of diagnostic severity for each disorder: Positive, Intermediate (at-risk), or Negative. Upon completion of the structured interview, the independent evaluator (IE) will assign interference scores to each positive diagnosis in order to determine primary and secondary diagnoses [80], based on a seven-point scale, with lower scores indicating less severity. Changes in coping skills will be assessed via a 34-item self-report questionnaire [105] that measures coping strategies (seeking social support, self-reliance/problem-solving, distancing, internalizing, and externalizing). The total score for this measure will be used in outcome analyses.

Changes in mental health symptoms (*e.g.*, aggression, conduct problems, anxiety, somatic symptoms) will be measured via parent [106], child [107,108] and teacher [106] multi-axial rating scales. Teachers will also provide changes in children’s grades and rate of academic productivity [109]. After all parent, child and teacher data are collected at pre- and post-, the IEs will complete a measure of functional impairment [110].

### Independent evaluator (IE) training and reliability

IEs will be advanced doctoral students in applied psychology who have been trained to a reliable standard on the use of diagnostic instruments by [name] and [name] following recommended guidelines through joint interviews, live observation, and discussion during the pre-study start-up meetings. IE reliability will be checked quarterly. Kappa coefficients will be computed, and a minimum of 0.85 will be required for each measure.

### Interventions

#### Primary prevention (universal interventions)

The use of SWPBIS in this study differs from other studies in that it focuses primarily on student mental health (*i.e.*, emotional and behavioral functioning). The focus of primary prevention strategies will be to prevent new cases of mild externalizing or anxiety problem behaviors by using school-wide (universal) strategies. A key intervention will be the development of a leadership team. The primary responsibility of the leadership team will be to develop, implement and formatively evaluate Tier 1 interventions. In the process, a set of school-wide expectations will be developed, explicitly taught to all students and promoted through the implementation of a school-wide motivation system. Specific rules and positive and negative consequences for student behavior in hallways, cafeteria, and playgrounds will be developed, taught to students, and implemented and monitored by school personnel. We expect that Tier 1 interventions will lead to improved school climate and perceived school safety. Improved school climate and perceived school safety will likely contribute to a decrease in the number of children who develop externalizing behavior problems, and also, anxiety problems. We will have two tiers in the proposed study: Tier 1 for universal interventions and Tier 2 for children who meet diagnostic criteria or are at risk for an externalizing or an anxiety disorder.

#### Secondary prevention (at-risk/high risk students)

The Coping Power Program (CPP) is a cognitive-behavioral, multi-component group intervention for elementary and middle school students at risk for externalizing behavior disorders. In addition to anger management, the CPP includes units on goal setting, emotional awareness, relaxation training, social skills training, problem solving, and handling peer pressure. The original CPP offers eight sessions for the first year of intervention and 25 sessions for the second year of intervention. We adapted the protocol based on qualitative (focus groups) and quantitative (acceptability) data from parents, children and teachers. We reduced CPP from the original 34-session program to a 14-session format to make it possible for counselors in busy under-resourced urban schools to run groups with CPP. Care was taken to maintain the key components (active ingredients) of the treatment, even though less time was dedicated to covering each Section. A previous shorter version of CPP (Anger Coping Program) has been found to be very effective with a group of aggressive boys [58,111].

Friends for Life (FRIENDS) is a group CBT intervention, based on a theoretical model, which addresses cognitive, physiological and behavioral processes that are seen to interact in the development and perpetuation of excessive anxiety. The original FRIENDS protocol consists of 10 (60-minute) weekly sessions and two booster sessions. In the present study, we have included the booster sessions in the regular protocol and added two more sessions in order to fit them into the typical class period (40 minutes), for a total of 14 sessions. The protocol has a parent component, which consists of two group sessions that focus on strategies to help parents cope with their own anxiety, reinforcement strategies and contingency management for children, and brief training in problem solving and communication skills.

### Data analytic plan

The statistical analyses for each of the study aims are described below: in addressing aim one, mean fidelity and its 95% confidence intervals for Tier 1 will be calculated using 20 randomly selected participants from each of the six schools during years three, four, and five (120 total per year). The 95% confidence intervals will be presented by C & C + C for all schools combined and for each school. Content and process fidelity data for Tier 2 will be obtained by scoring 14 video recorded sessions per each of the treatment groups. Perception of School Climate (aim two) during year one will be surveyed by a randomly selected sample of teachers, support staff and administrators from each participant school. The randomly selected sample will consist of similar proportion of teachers, support staff and administrators within each school. The questionnaire [101] will be completed at the end of years one, two, three, four, and five. This 31-item, 5-point Likert type scale checklist has four factors. Each factor’s total score will be analyzed separately. School personnel no longer present in the school during subsequent years will be replaced.

The general analytical approach for testing our hypotheses will be the Laird and Ware mixed effects model [112] and the Generalized Estimating Equation (GEE) approaches [113,114]. Mixed effects and GEE are statistical approaches based on regression techniques for analyzing correlated data collected repeatedly from the same subject. The study design will allow us to examine the between- subjects effect related to the two levels of support, and a within-subjects effect corresponding to time points (five time points), as well as a type of support (C, C + C) by time interaction effect. These analyses will be conducted using SAS Proc Mixed, which utilizes the mixed effects models, and SAS Proc Genmod, which utilizes GEE [115]. Both the mixed effects model and GEE approaches allow estimation of fixed effect parameters such as time, and time by treatment interaction. If the interaction term is significant, it indicates that change in school climate and/or reduction in ODRs over time is significantly different between the two levels of support. If the interaction term is statistically not significant, the changes over time for the two primary outcomes will be presented by the time effect only, which represents both levels of support. The advantage of utilizing these methods is that all information available from each student is used, including variables with missing observations. In the proposed analyses, we will consider students measured within classes are correlated and will be nested within classes. Nested analysis will be chosen as part of Proc Mixed and Proc GEE, as such, the intraclass ‘intracluster’ correlation (ICC) will be part of the overall variance covariance matrix.

Changes from pre- to post- implementation in diagnostic status, symptom severity and impairment level, coping skills and academic productivity during Implementation across all schools, regardless of level of support, will be analyzed using McNemar tests. For each of the listed primary outcomes, a series of 2X2 tables will be constructed to test changes from pre- to post- in the pertinent categories using McNemar tests. Alpha level will be adjusted to 0.025 based on Bonferroni criteria for multiple comparisons. We will also use McNemar tests to test the hypothesis that the pre- to post- level of improvement in diagnostic status, symptom severity, impairment level, coping, and academic productivity obtained during Implementation will be maintained during Sustainability among schools receiving C + C.

We would like to determine whether pre- to post- improvement in diagnostic status, symptom severity, impairment level, and academic productivity differ by support condition during the implementation phase. In addressing this research question, and for the sake of simplifying the statistical analysis, each student will be categorized as either improved or not improved based on change from pre- to post-. A category one will be assigned if a student’s diagnostic status, for example, changes either from positive to intermediate, intermediate to negative, or positive to negative. Otherwise a score of zero will be assigned. Similar coding will be used for symptom severity, coping, impairment level, and academic productivity. We will use chi-squared tests to compare the proportion of (yes/no) for each of the primary outcomes between C and C + C type of supports. To examine changes in the rate of ODRs between baseline and follow up during each school year, the number of students with at least one ODR will be defined at baseline and at the follow up and a 95% confidence interval for such changes will be constructed for each of the five years.

In addressing aim three, school climate scores and the proportion of out-of school suspensions (number of suspension divided by number of students) served at the school during the previous academic year (*i.e.*, before implementation of Tier 1) will be compared to school climate scores (using the two independent sample t-test), and school suspensions for each subsequent project year (using Chi-squared test) respectively. For Tier 2, the proportion of children at baseline who are found to have unmet need for mental health services (*e.g.*, children found to have an externalizing or anxiety disorder at the intermediate or clinical level via the DISC-IV and who have not received mental health services as measured via the SACA) will be compared to the proportion of children with unmet need for mental health services in subsequent years (using Chi-squared test). In order to obtain a measure of unmet need at baseline, we will interview parents to assess the presence of disorders and service utilization at one year prior to the assessment and at the time of the assessment. For each subsequent cohort of children, we will interview parents about presence of disorder and service utilization only at the time of the assessment. Comparison of the proportion of unmet need between each subsequent year to the baseline proportion will be compared using Chi-square test.

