### Sample size justification and statistical power

Sample size estimation was based on addressing the primary outcome, the participants’ diagnostic status (aim two). The statistical analysis will be McNemar tests for two correlated proportions (pre/post) between two groups. With a sample size of 300 students, the statistical test achieves 92% power to detect an odds ratio of three using a two-sided McNemar test with a significance level (α ) of 0.01. The odds ratio is equivalent to a difference between two paired proportions of 0.25, which occurs, for example, when the proportion among students diagnosed with a Positive anxiety/externalizing disorder at pre and improved to Intermediate at post (cell 1,2 in the 2X2 McNemar table) is 0.425 and the proportion among students diagnosed without Positive anxiety/externalizing disorder who became either Intermediate or Positive at post (cell 2,1 in the 2X2 McNemar table) is 0.175. Therefore, the proportion of discordant pairs is 0.60. We adjusted α level to 0.01 to account for the multiple 2X2 McNemar testing. We need to recruit six schools, grades four to eight,to be able to enroll 300 evaluable students who meet inclusion criteria. We assumed that the observed changes in students’ diagnostic status within schools are independent based on an evaluation of the FRIENDS program, in which ‘schools’ level accounted for less than 5% of the total variance across dependent measures.

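### The Tier 1 plan counts school climate and ODRs as two primary outcomes, but climate is analysed as four separate factors, so at least five support-by-time tests carry no stated multiplicity control.

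*Protocol article*

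**What the plan says.** Four statements bear on the point.

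- **How climate is measured.** The School climate section lists four factors (Skill Instruction, Support for Staff, Staff Respect for Students, Safety) and adds: "We will use all four factors in the analyses". The Data analytic plan confirms: "Each factor’s total score will be analyzed separately". It names no overall score and no lead factor.
- **How the Tier 1 comparison is read.** The Data analytic plan fits mixed models and GEE with a support-by-time interaction, and interprets it thus: "If the interaction term is significant, it indicates that change in school climate and/or reduction in ODRs over time is significantly different". The comparison meant is C against C + C. For a non-significant result the plan pools the arms: "the changes over time for the two primary outcomes will be presented by the time effect only".
- **Where alpha is adjusted.** In the paragraph on pre/post McNemar tests of the child outcomes: "Alpha level will be adjusted to 0.025 based on Bonferroni criteria for multiple comparisons". In the sample size section: "We adjusted α level to 0.01 to account for the multiple 2X2 McNemar testing". No level is attached to the interaction models.
- **What is primary.** The Data analytic plan gives that status to climate and ODRs, and in its next paragraphs applies the same word to the Tier 2 child outcomes. The sample size section says: "Sample size estimation was based on addressing the primary outcome, the participants’ diagnostic status (aim two").

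**The concern.** The stated count of primary outcomes does not match the stated analyses. One of the two outcomes is four tests, so following the article literally gives five interaction tests under an interpretation that joins climate and ODRs by and/or. The text speaks of a single interaction term and uses it to choose between reporting by support level and reporting a pooled time effect. It does not say what is concluded about climate if one factor's interaction is significant and three are not. The factors measure different things: Support for Staff could respond to coaching while Safety does not.

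A chance result would also carry forward. The cost analysis under aim four envisages cost-effectiveness ratios for further outcomes, school climate among them, where the comparison shows significant improvement. A false positive on a single factor could therefore produce a ratio intended to inform districts and policy makers about the value of extra support.

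**Working it through.** **Plan's own figure.** There is none to reproduce. The article gives no error rate, alpha or power for the Tier 1 interactions. Its only power calculation concerns the Tier 2 McNemar test on diagnostic status and does not enter here.

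**Inputs.**
- From the article: 4 climate factors, each analysed separately, plus ODRs. With one interaction test each, k = 4 + 1 = 5.
- Assumed, because the article gives neither: a two-sided level a per test (0.05, or 0.025 if the Tier 2 level were carried over) and a common correlation r between test statistics (0 to 0.8).
- Also assumed: each single test holds its nominal level, and each interaction can be represented by one normal statistic.

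**Independent tests.** P(at least one false positive) = 1 − (1 − a)^k.
- The count the text implies, k = 2: at 0.05, 1 − 0.95² = 9.75%; at 0.025, 1 − 0.975² = 4.9%.
- Climate alone, k = 4: at 0.05, 1 − 0.95⁴ = 18.5%; at 0.025, 1 − 0.975⁴ = 9.6%.
- Climate plus ODRs, k = 5: at 0.05, 1 − 0.95⁵ = 22.6%; at 0.025, 1 − 0.975⁵ = 11.9%.

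**Correlated tests.** With z the two-sided critical value for a, φ and Φ the standard normal density and distribution function, and t a shared standard normal component:

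P = 1 − ∫ φ(t) [Φ((z − √r·t)/√(1 − r)) − Φ((−z − √r·t)/√(1 − r))]^k dt

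Numerical integration gives:

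| k | a | r = 0 | r = 0.5 | r = 0.8 |
|---|---|---|---|---|
| 4 | 0.05 | 18.5% | 15.6% | 11.4% |
| 5 | 0.05 | 22.6% | 18.3% | 12.7% |
| 5 | 0.025 | 11.9% | 9.8% | 6.9% |

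If the four factors are correlated with each other but ODRs are independent of them, simulation at 0.05 per test gives 19.8% for r = 0.5 and 15.8% for r = 0.8, inside the five-test range.

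**Would the existing 0.025 suffice?** It equals 0.05/2, so it fits two tests. Across five tests the Bonferroni bound is 5 × 0.025 = 12.5%.

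**After correction.** Bonferroni over five tests uses 0.05/5 = 0.01 each: 1 − 0.99⁵ = 4.9% if independent, and at most 5% under any correlation. Holm has the same guarantee and is never less powerful; its successive thresholds are 0.01, 0.0125, 0.0167, 0.025 and 0.05.

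**The case against.** Four objections deserve an answer.

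1. **The and/or sentence is not a decision rule.** A reader might infer that one significant factor formally establishes a climate effect. The article does not say so. The sentence explains what a significant interaction would mean, and separate analysis of the factors fits factor-specific reporting. This objection stands. What remains is that it is the only criterion given for these models, and it is written for two outcomes.

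2. **No single error rate can be assigned to this trial.** A reader might infer a flat false-positive rate of about 18%. That figure needs an alpha of 0.05, a correlation of 0.5 across five tests and valid single tests, none of which the article supplies. Validity is itself uncertain: six schools were randomised, Table 1 implies three per arm, and the model is described as nesting students within classes. This stands too, and only a conditional range is defensible.

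3. **Climate may not be confirmatory.** The trial is sized on diagnostic status, which the sample size section calls the primary outcome. If that governs, reporting climate subscales separately is ordinary secondary analysis. This is a fair reading, but the Data analytic plan explicitly says otherwise, so the conflict has to be settled in the text.

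4. **Testing order and per-test alpha usually belong in the SAP.** They do, and their absence alone would be no finding. Here the article itself states the count and the analyses, and they disagree. It also sets multiplicity levels, but only for Tier 2.

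**Conclusion.** The concern holds in a limited form. The article names two primary Tier 1 outcomes but specifies at least five interaction tests, with no multiplicity control tied to them. Under the assumptions above, the chance of at least one false C versus C + C difference is about 13% to 23% at 0.05 per test, and about 7% to 12% at 0.025. Both ranges lie above 5% throughout. They illustrate the size of the problem and are not the trial's actual error rate, which also depends on how the school clusters are handled. The documents do not support calling the and/or sentence a formal success rule. The inconsistency should be corrected before analysis, but it does not undermine the design.

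**What to change.** In the Data analytic plan:

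- Define the Tier 1 family as the four climate-factor interactions plus the ODR interaction, and test it by Holm at an overall two-sided 0.05. Alternatively, prespecify one climate score as primary, test it with ODRs by Holm (0.025, then 0.05), and treat the remaining factors as secondary.
- Replace the and/or sentence with conclusions specific to each outcome and factor, and apply the rule for non-significant interactions in the same way.
- Reconcile which outcomes are primary between the interaction-model paragraph, the McNemar and chi-squared paragraphs, and the sample size section.

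A joint multivariate test of the four factors is not recommended. At school level, a Hotelling test on six schools has 4 and 6 − 4 − 1 = 1 degrees of freedom, with a critical F of about 225 at 0.05. Leaving school out to avoid this would ignore the unit of randomisation.

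The change costs wording only and needs no new data. The price is that an isolated effect on a single factor becomes harder to claim.
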